# PITCH (pediatric infratentorial tumors – hydrocephalus-related complications) registry study design: observational, prospective, multicenter study evaluating the number of surgeries associated with the treatment of hydrocephalus secondary to infratentorial tumors in childhood and adolescence

**DOI:** 10.1007/s00381-026-07282-0

**Published:** 2026-05-08

**Keywords:** Endoscopic third ventriculostomy, Ventriculoperitoneal shunt, External ventricular drainage, Treatment outcomes

## Abstract

**Introduction:**

Posterior fossa tumors are the most common solid pediatric neoplasms, and more than 60% of these tumors are associated with hydrocephalus, which can be managed using different strategies, including endoscopic third ventriculostomy (ETV), ventriculoperitoneal shunt (VPS), external ventricular drainage (EVD), or direct tumor resection without CSF diversion. The safest and most effective drainage method remains controversial, and most available studies are limited to single-center retrospective analyses, often constrained by small sample sizes. Therefore, multicenter prospective studies are needed to determine the optimal treatment strategy.

**Methods:**

This is a prospective, multicenter cohort study conducted across more than 20 pediatric neurosurgery centers in Latin America. Patients will be allocated into four groups according to the treatment selected for hydrocephalus (ETV, EVD, VPS, or resection). The primary outcome will be the number of surgical interventions related to the treatment of hydrocephalus during the follow-up period. Secondary outcomes will include mortality, infection, and other clinically relevant complications, analyzed as complementary endpoints. Patients will be followed prospectively for up to 12 months after the index procedure, defined as the intervention performed for the treatment of hydrocephalus, and each group will include at least 50 patients.

**Conclusion:**

The REDCap online platform will be used for data collection in the PITCH study, enabling prospective data acquisition across multiple centers in Latin America. This will allow comparison of treatment modalities for obstructive hydrocephalus secondary to posterior fossa tumors (ETV, EVD, VPS, and resection) and evaluation of their impact during the first year after diagnosis.

## Introduction

Among all childhood cancers, central nervous system (CNS) tumors account for 20.7%, second only to leukemias; however, among solid tumors, they are the most common, and of these, infratentorial tumors represent 60% of cases [1]. Posterior fossa tumors are associated with hydrocephalus [2], specifically non-communicating hydrocephalus, since most of these tumors cause direct or indirect obstruction of the fourth ventricle and/or its outflow pathways [3–5].

In a study of 117 children with posterior fossa tumors, Culey et al. [4] reported hydrocephalus in 83% of the patients. Dias MS et al. [5] concluded that one-quarter to one-third of infants with posterior fossa tumors were associated with hydrocephalus requiring diversion.

Although it may be intuitive to think that obstructive hydrocephalus can be treated with tumor resection, several factors predispose to persistent hydrocephalus after tumor removal: young age, preoperative hydrocephalus, midline tumor location, metastases, subtotal resection, tumor pathology, use of external ventricular drains, and postoperative complications [6].

There are several clinical contexts related to the treatment of hydrocephalus secondary to posterior fossa tumors; therefore, various management strategies for hydrocephalus secondary to infratentorial tumors have been described, such as endoscopic third ventriculostomy (ETV), ventriculoperitoneal shunt (VPS), external ventricular drainage (EVD), or direct resection of the lesion without other diversion methods [7–10]. However, each of these strategies has risks and benefits associated with the therapeutic decision made for each patient, and part of the difficulty in choosing a safer treatment method is due to the multiple outcomes selected in studies with different methodologies, making comparison between studies and between hydrocephalus treatment methods very difficult.

Thus, based on the collaborative effort presented, we identified the need for a prospective multicenter study focusing on the main treatment strategies for hydrocephalus secondary to posterior fossa tumors in children. The PITCH study aims to compare different treatment modalities for obstructive hydrocephalus secondary to posterior fossa tumors (endoscopic third ventriculostomy, external ventricular drainage, ventriculoperitoneal shunt, and tumor resection), considering the number of surgeries related to hydrocephalus treatment and its associated complications within the first year after the initial procedure performed to treat hydrocephalus, as well as mortality and infection rates.

## Methods

A prospective, multicenter, controlled cohort study will be conducted. The primary outcome will be the number of surgical interventions related to the treatment of hydrocephalus during the follow-up period, as it directly reflects treatment failure and holds significant clinical relevance. Secondary outcomes will include mortality, infection, and other clinically relevant complications, which will be analyzed as complementary endpoints. The study was approved by the Scientific Committee of the Instituto de Oncologia Pediátrica (IOP/GRAACC) and by the Ethics Committee of the Universidade Federal de São Paulo (UNIFESP), as well as by the ethics committees of all participating centers. Patients will be included in the study after obtaining written informed consent from their legal guardians and assent from patients under 18 years of age diagnosed with hydrocephalus secondary to posterior fossa tumors, confirmed by imaging studies (computed tomography (CT) and magnetic resonance imaging (MRI)), and who will undergo surgical resection of the posterior fossa lesion.

### Characteristics of the inclusion and exclusion criteria

The patients included will be under 18 years old with a diagnosis of hydrocephalus secondary to a primary tumor of the central nervous system (CNS) located in the posterior fossa, characterized by clinical data and radiological imaging (CT or MRI).

Hydrocephalus secondary to posterior fossa tumor will be characterized when the patient presents a tumor in the posterior fossa causing obstruction of cerebrospinal fluid circulation and enlargement of the lateral ventricles and the third ventricle, with such enlargement documented by imaging exams such as cranial CT or MRI, which must identify, in addition to ventricular enlargement, the presence of enlargement of the temporal horns of the lateral ventricles (> 2 mm) and transependymal edema in the frontal and/or occipital horns of the lateral ventricles. In addition, the patient must present signs and symptoms related to increased intracranial pressure (ICP), such as headache, irritability, vomiting, strabismus and/or unilateral or bilateral sixth cranial nerve palsy, papilledema, bradycardia, arterial hypertension, and altered level of consciousness (drowsiness, stupor, or coma).

Participating centers will be those that offer, through the public health system and/or the supplementary health system, surgical treatment for patients under 18 years of age with posterior fossa tumor. Patients who were initially treated for hydrocephalus in an external center may be included, provided that all necessary information for inclusion in the study is available.

Patients will be excluded from the study if they have lesions in sites other than the posterior fossa as the main focus, patients who have previously undergone surgical resection of posterior fossa tumors, patients without hydrocephalus associated with posterior fossa tumor, patients with posterior fossa tumors and hydrocephalus who will not undergo surgical resection of the lesion (for example, diffuse intrinsic pontine glioma), or cases in which only biopsy of the lesion is considered, patients who refuse to participate in the study, and patients whose data regarding hydrocephalus and its characterization cannot be recovered with the level of detail necessary for the study.

## Results

Participant recruitment will occur through spontaneous demand and may take place in the immediate postoperative period of the hydrocephalus surgery, but it must occur, without exception, in the preoperative period for the tumor surgery, requiring the signing of the Informed Consent Form. Data collection will occur according to the child’s routine clinical care.

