### Outcome assessment

The primary outcome of this study will be the number of reintervention surgeries for the treatment of hydrocephalus after the index surgery for hydrocephalus treatment, which will be chosen at the discretion of each participating center and the attending physician responsible for the patient’s initial treatment.

Patients will be included after signing the Informed Consent Form and/or Assent Form and meeting the inclusion and exclusion criteria. Their data will be anonymously entered into the REDCap software (Fig. 1) for prospective follow-up. Each participating center will be recognized by a specific identifying number. Once the patient is selected to participate in the study, they will be prospectively followed, and each outcome event may be recorded in real time or at the predetermined follow-up times of 1 month postoperatively, 3 months, 6 months, 9 months, and 12 months, always considering day zero as the day on which the hydrocephalus treatment was performed.

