**Fig. 1 Fig1:**
[figure not shown]
Representative screenshot of the online registry (https://redcap.unifesp.br/), referring to the general data entry and the patient’s inclusion in the study. **A** Login and password that each center receives to begin the data entry. **B** Selection of the research arm. **C**, **D** An overview of the data used

A separate confidential record will be maintained with the identifying information—full name of the patient and legal guardian, date of birth, sex, ethnicity, identifying number of the participating center, local hospital record, and REDCap ID—to ensure that duplication of patients in the study does not occur.

In the preoperative survey, the following information will be collected (Table 1).

**Table 1 Tab1:** Information on preoperative variables

Variable	Definition/categories
Patient identification number	Unique patient code
Age	In years
Date of birth	dd/mm/yyyy
Date of diagnosis	Date of the initial exam (CT, MRI, or transfontanellar ultrasound) documenting posterior fossa tumor + hydrocephalus
Lesion topography	Main location (> 50% of volume): • 4th ventricle • Cerebellar hemisphere • Cerebellar vermis • Cerebellopontine angle • Brainstem
Tumor size	Largest axial diameter (mm)
Histological classification	Preoperative diagnosis (if available) + pathological confirmation (e.g., astrocytoma, ependymoma, medulloblastoma, ATRT)
Malignancy grade	WHO 2021 classification (adjusted after final pathology report)
Clinical signs/symptoms	Headache, vomiting, dizziness, gait disturbance, diplopia, facial palsy, choking, etc.
Leptomeningeal spread	Leptomeningeal thickening/enhancement on contrast-enhanced MRI
Hydrocephalus on imaging	Radiological criteria: • Increased Evans index • Temporal horn dilation (> 2 mm) • Ependymal transudation • Ballooning of the 3rd ventricle • “Beaten silver” appearance • Empty sella • Concavity of the 3rd ventricle floor
Type of initial intervention	ETV, EVD, VPS, or tumor resection + date of procedure

For each procedure chosen as a management strategy for hydrocephalus, its particularities will be considered (Table 2).

**Table 2 Tab2:** Information on the modalities chosen for the treatment of hydrocephalus secondary to posterior fossa tumor

Procedure	Specific variables
VPS	• Location of proximal catheter (frontal/occipital) • Type of valve (fixed, adjustable, flow-regulated) • Brand (national/imported) • Antibiotic impregnation (yes/no) • Distal catheter trimming (yes/no)

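### Entry timing differs by arm: diversion children may enrol after day zero, resection children must enrol before it, so early deaths and losses of eligibility can be missed in the diversion arms only

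*Protocol article*

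**What the plan says.** Four rules in the protocol article bear on this point.

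- **When a child may enrol.** The recruitment paragraph under Results lets enrolment "take place in the immediate postoperative period of the hydrocephalus surgery, but it must occur, without exception, in the preoperative period"; the operation meant in the last words is the tumor operation.
- **Who may enrol.** The section on inclusion and exclusion criteria states: "Patients who were initially treated for hydrocephalus in an external center may be included", on condition that the necessary information is available. It gives no maximum time from that outside procedure to consent. It excludes children for whom resection is not planned. It also excludes "patients whose data regarding hydrocephalus and its characterization cannot be recovered with the level of detail necessary for the study", a rule that covers all arms.
- **What counts as the index.** Table 1 lists the initial intervention as "ETV, EVD, VPS, or tumor resection + date of procedure". Table 2 defines the resection arm by the absence of any drainage device before or during surgery, and records EVD use as either preoperative or intraoperative.
- **Where the clock starts.** Outcome assessment fixes the visit schedule "always considering day zero as the day on which the hydrocephalus treatment was performed". Prospective follow-up starts once the child has been selected.

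The Statistical analysis section and the limitations paragraph of the Discussion plan ANCOVA, multivariable regression and propensity-score methods. The last two are aimed at non-random choice of treatment.

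**The concern.** The study exists to compare four initial strategies, so a child's chance of being in the data should not depend on the strategy in a way tied to outcome. Here it can. A child who is diverted and then dies, or stops being a candidate for resection, before consent never enters. A resection-arm child with the same early event has already consented, and the event counts. For a late entrant, the interval from day zero to consent is time in which death could not have been observed, yet it is counted as follow-up.

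The endpoints exposed are the article's own. Mortality and infection are named secondary outcomes. Table 3 defines failure of initial treatment as a further hydrocephalus operation or a related death, recorded as time to failure. It also lists upward herniation after EVD and new tumor hemorrhage after a diversion, both of which could occur before consent. The primary reintervention count starts at the same day zero.

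**Working it through.** **Entry relative to day zero, by type of index**

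| Index procedure | Is the index the tumor surgery? | Entry after day zero possible? |
|---|---|---|
| ETV or VPS | No | Yes |
| EVD placed before tumor surgery | No | Yes |
| EVD first placed at tumor surgery | Same operation | No |
| Resection without drain | Yes | No |
| Diversion at an outside center | No | Yes, with no stated interval |

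The asymmetry follows from the stated rules alone.

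**Size for mortality.** The article gives no mortality, no index-to-consent interval and no share of late entrants, so these inputs are assumptions. Let *m* be the true 12-month mortality, equal in all arms; *e* the part of it falling between index and consent; and *g* the share of diversion children who would enrol late. The children lost are *g·e*, and

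observed diversion mortality = (*m* − *g·e*) / (1 − *g·e*).

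With *m* = 12%, resection shows 12% and diversion shows:

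| *g* | *e* | Calculation | Observed | Ratio to resection |
|---|---|---|---|---|
| 0.5 | 1 point | 0.115 / 0.995 | 11.6% | 0.96 |
| 1 | 2 points | 0.10 / 0.98 | 10.2% | 0.85 |
| 0.5 | 4 points | 0.10 / 0.98 | 10.2% | 0.85 |
| 1 | 4 points | 0.08 / 0.96 | 8.3% | 0.69 |

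A wider grid takes *m* from 5% to 15%, 10% to 50% of deaths before consent, and *g* from 0.5 to 1. Resection then appears 1.04 to 1.95 times as lethal as diversion with no true difference.

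**Sensitivity of the primary test.** The article's sample size reproduces. With *f* = 0.25, α = 0.05, four groups and one covariate, the smallest N with 80% power is 179, with F(3,174) and power 0.801; 179 / 0.9 = 198.9, so 199, stated as about 200. Nothing is wrong there. To gauge how far selection could mislead that test, suppose no true difference and a spurious shift of *d* SD in the resection mean against three equal diversion arms. Then *f* = *d*·√3/4. For *d* = 0.2, *f* = 0.087 and the noncentrality is *f*²N = 0.0075 × 179 = 1.34. The false-positive rate is 13.9%, against 5% nominal. For *d* = 0.1 it is 7.0%. Neither the size nor the sign of *d* can be taken from the documents.

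**The case against.** Several points on the other side stand.

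- Late entry is permitted, not required, and is described as immediately postoperative. A child consented before diversion is unaffected, and a short gap holds few events. It is also arguable that the outside-center clause is bounded by the same words. But the article does not say so, and the two sections need reconciling.
- A reader might infer that the diversion arms consist only of survivors who reached tumor surgery. The text does not support that. Resection has to be planned and consent has to precede it; nothing removes an enrolled child who dies first. Nor is deterioration alone an exclusion.
- The EVD arm is only partly affected, because of intraoperative placement.
- The primary analysis is an ANCOVA of counts with no person-time denominator. Table 3 records the date of each reintervention, so those before consent can be counted in children who do enrol. Immortal time in the strict sense bears mainly on mortality and time to failure; for the count, the issue is who enters.
- One might infer that outside-center children are referred because the first procedure failed. The documents do not say this. If it happens, it would raise the diversion count, against the effect of survivor selection.
- At 50 per arm, 12% against 8.3% is 6 against about 4 deaths (50 × 0.083 = 4.2), on a secondary outcome.

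The statistical analysis plan is not shown and may provide for delayed entry. It cannot restore children who were never enrolled or logged, and the planned regression and propensity methods balance only those who were.

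**Conclusion.** The point holds as a statement about what the entry rules allow. The diversion arms can include children selected for having survived, and remained candidates for resection, until consent, while the same early events count in the resection arm. This truncation favours diversion on mortality and time to failure. For infection, complications and the primary reintervention count, bias is possible and its direction unknown.

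The mortality ratio of 0.96 to 0.69 rests on an assumed 12% mortality and on assumed late-entry shares and timing. The 0.69 end needs every diversion child to enrol late and one third of deaths to precede consent, so it is close to a worst case and should not be read as an estimate. The planned sample size is not affected.

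**What to change.** 1. Reconcile the recruitment paragraph with the outside-center clause, and state a maximum index-to-consent interval that applies to all children.
2. Record the date of consent relative to the index procedure.
3. Keep an anonymised log of all index diversions at participating centers, including children who died or lost eligibility before consent, so that the loss can be counted.
4. Analyse mortality and time to failure with delayed entry at consent. This assumes that time of entry is unrelated to later risk, given the covariates. Children whose first failure precedes consent contribute nothing to the time-to-failure analysis and should be reported separately.
5. Delayed entry does not repair the reintervention count. For that outcome, add a pre-specified analysis restricted to children whose index procedure was at a participating center and who were identified at that procedure, with externally treated children shown separately.

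The cost is protocol wording, one date field and a short log. The restricted analysis will hold fewer diversion-arm children, which matters against the target of at least 50 per group; the documents do not allow the shortfall to be estimated.

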### Outcome assessment

The primary outcome of this study will be the number of reintervention surgeries for the treatment of hydrocephalus after the index surgery for hydrocephalus treatment, which will be chosen at the discretion of each participating center and the attending physician responsible for the patient’s initial treatment.

Patients will be included after signing the Informed Consent Form and/or Assent Form and meeting the inclusion and exclusion criteria. Their data will be anonymously entered into the REDCap software (Fig. 1) for prospective follow-up. Each participating center will be recognized by a specific identifying number. Once the patient is selected to participate in the study, they will be prospectively followed, and each outcome event may be recorded in real time or at the predetermined follow-up times of 1 month postoperatively, 3 months, 6 months, 9 months, and 12 months, always considering day zero as the day on which the hydrocephalus treatment was performed.

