## Sample size calculation

The sample size calculation was performed considering the number of surgeries as the primary outcome, which is the main variable of interest in this clinical study. The primary analytical objective is to compare the effect of four treatment strategies on this outcome, with adjustment for age as a relevant covariate.

For sample size estimation, G*Power software version 3.1.9.6 [11] was used, as described by Kang [12], adopting the *F*-test family, specifically the ANCOVA option: fixed effects, main effects, and interactions, in an a priori analysis. This approach is widely used for comparisons between groups with adjustment for covariates in clinical studies [13–15]. A medium effect size (*f* = 0.25), a significance level of 5% (*α* = 0.05), and a statistical power of 80% (1 − *β* = 0.80) were assumed, as recommended to ensure adequate ability to detect clinically relevant differences. The model included four comparison groups and one covariate (age). Based on these parameters, a minimum total sample size of 179 participants was estimated. Assuming a 10% loss to follow-up, the total sample size would be approximately 200 participants, corresponding to about 50 individuals per group, resulting in a test with degrees of freedom *F*(3,174) and a statistical power of approximately 80%.

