## Discussion

The discussion regarding the safest and most efficient drainage method, and when to perform it (before, during, after tumor resection, or whether to simply monitor hydrocephalus after resection without the need for perioperative diversion), remains controversial in the literature [16–19], since each method presents characteristic advantages and disadvantages that also depend on hospital infrastructure [7].

Several studies reported in the literature are restricted to a single center [3, 7, 8, 17–21], and most are limited by the small number of participants [22]. Thus, multicenter, prospective, and randomized studies in this area are necessary [9, 16, 22].

Described in 1923 by William Mixter [23], endoscopic third ventriculostomy provides the benefits of treating hydrocephalus at presentation and reducing its incidence after resection, in addition to avoiding the placement of drains and enabling tumor resection under low intracranial pressure conditions [3, 6].

Moreover, the procedure reduces intraoperative and late complications associated with EVD and VPS placement and promotes the “physiological” restoration of cerebrospinal fluid circulation [21]. However, it is a procedure that may be associated with complications such as hemorrhage, bradycardia, hemiparesis, memory dysfunction, diabetes insipidus, epilepsy, infection, and fistula [21].

Tamburrini G et al. [24], in a study conducted with 30 children, reported that factors such as extent of tumor resection, degree of hydrocephalus, histology, and tumor location were not associated with ETV success. Srinivasan et al. [8] recommended the procedure only in cases of symptomatic hydrocephalus and reported a higher failure rate associated with ependymoma.

VPS is one of the alternatives for the treatment of hydrocephalus [25]. However, it may present complications such as infection, ascites, visceral perforation, hemorrhage, and peritonitis [21], as well as other rarer complications such as device migration or extrusion [26].

Metastatic cell dissemination, such as in medulloblastoma, may occur through the VPS catheter [27–29]. In patients under 19 years of age with hydrocephalus secondary to posterior fossa tumor, ETV failure occurs earlier when compared to VPS, although cumulative failure is lower with ETV (21%) than with VPS (29%) [30].

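### The primary ANCOVA and its sample size leave out centre although treatment choice depends partly on centre; if outcomes also correlate within centre, type I error exceeds 5% and a centre-adjusted test falls short of 80% power

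*Protocol article*

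**What the plan says.** All places are in the protocol article.

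- **Outcome assessment:** the index hydrocephalus procedure "will be chosen at the discretion of each participating center and the attending physician" responsible for the child's initial treatment. Each centre has an identifying number in the database.
- **Abstract, Methods:** the study is "conducted across more than 20 pediatric neurosurgery centers in Latin America".
- **Sample size calculation:** the primary objective is to compare four strategies with adjustment for age. "The model included four comparison groups and one covariate (age"), and on that basis "a minimum total sample size of 179 participants was estimated", with F(3,174).
- **Statistical analysis:** the primary outcome is compared by ANCOVA. Multivariable models for further covariates are assigned to the secondary outcomes.
- **Discussion:** on choosing a drainage method, "each method presents characteristic advantages and disadvantages that also depend on hospital infrastructure". As a guard against selection bias it adds multivariable regression and propensity score methods. The kinds of covariate named are demographic, clinical and radiological.
- **Inclusion and exclusion criteria:** children whose hydrocephalus was first treated at an outside centre may be enrolled if the required information is available.

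**The concern.** When a centre helps decide which procedure a child receives, arm and centre become associated. The outcome, the number of further operations for hydrocephalus, is also the result of a surgical decision, so it may depend on local practice as well. Centre would then act in two ways. As a confounder, it lets a difference in local habits appear as a difference between ETV, EVD, VPS and resection. As a source of correlation, it makes standard errors that assume independent children too small. Adjusting for age removes neither effect, and recruiting more children does not remove the confounding.

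The comparison of the four strategies is the purpose of the study, and the primary test is where this would show.

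**Working it through.** **1. The plan's own figure.** Inputs from the sample size section: f = 0.25, α = 0.05, power 0.80, four groups, one covariate. With noncentrality λ = f²N, df1 = 3 and df2 = N − 4 − 1, the smallest N with power of at least 0.80 is 179. There df2 = 174 and power = 0.8015. Allowing for 10% loss, 179/0.9 = 198.9, so 199, which agrees with the stated figure of about 200. The calculation is correct for independent patients.

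**2. What F(3,174) implies.** 179 − 4 − 1 = 174, so no degrees of freedom go to centre. With 20 centres as fixed effects, the denominator would be 174 − 19 = 155.

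**3. Limiting case: one treatment per centre.** Assumptions: 20 centres, m = 179/20 = 8.95 children each, design effect DE = 1 + (m − 1) × ICC. The article gives no ICC, so a range is used. Power is taken at effective N = 179/DE.

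| ICC (assumed) | DE | Effective N | Power, df2 = 174 | Power, df2 = 20 − 4 = 16 |
|---|---|---|---|---|
| 0.02 | 1.16 | 154 | 0.73 | 0.63 |
| 0.05 | 1.40 | 128 | 0.64 | 0.54 |
| 0.10 | 1.80 | 100 | 0.53 | 0.43 |
| 0.20 | 2.59 | 69 | 0.38 | 0.31 |

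**4. Partial clustering, by simulation.** N = 179, 20 centres, normal outcome with total variance 1, f = 0.25 under the alternative, 1,500 null and 1,000 alternative runs per setting. Each centre's treatment mix is drawn from a symmetric Dirichlet distribution with total concentration 4 (moderate) or 1 (strong). With α the concentration divided by 4, two children at one centre share a treatment with probability (α + 1)/(4α + 1). That is 2/5 = 0.40 for moderate and 1.25/2 = 0.625 for strong clustering, against 0.25 with no clustering and 1 in the limiting case.

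Type I error of the ANCOVA without centre:

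| Treatment clustering | ICC 0.02 | 0.05 | 0.10 | 0.20 |
|---|---|---|---|---|
| None | 0.049 | 0.044 | 0.055 | 0.048 |
| Moderate | 0.055 | 0.069 | 0.072 | 0.123 |
| Strong | 0.063 | 0.089 | 0.125 | 0.241 |
| One treatment per centre | 0.079 | 0.142 | 0.238 | 0.425 |

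The simulation standard error near 5% is √(0.05 × 0.95/1500) = 0.006, so moderate clustering at ICC 0.02 cannot be told apart from 5%.

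Power with centre as a fixed effect:

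| Treatment clustering | ICC 0.02 | 0.05 | 0.10 | 0.20 |
|---|---|---|---|---|
| None | 0.758 | 0.760 | 0.774 | 0.860 |
| Moderate | 0.622 | 0.646 | 0.720 | 0.744 |
| Strong | 0.432 | 0.433 | 0.445 | 0.495 |

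Across the same settings and the limiting case, the rejection rate under the alternative for the ANCOVA without centre stays between 0.77 and 0.82.

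**5. Sensitivity to the assumed mix.** Runs with 20 centres of exactly 9 children at ICC 0.05–0.10 gave type I error of 4–5% (no clustering), 5–8% (moderate) and 11–15% (strong). Power with centre fixed effects was 66–70% (moderate) and 32–37% (strong). Another 2,000 runs, with each centre using its preferred strategy in about 85% of cases, gave 8% at ICC about 0.04 and 15% at about 0.10. In the limiting case, approximating type I error by P(F > Fcrit/DE) gives 13–14% at ICC 0.05, in line with the simulated 0.142.

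**The case against.** The strongest reply has four parts.

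**Treatment is not assigned by centre.** The attending physician shares the choice, and for some children an outside centre made it. Treatment may therefore vary within centres, and one treatment per centre is only a limiting case. This stands. With no clustering of treatment, type I error stays at 0.044–0.055 for ICC up to 0.20, so there is no material error.

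**The documents show neither the correlation nor the clustering.** This also stands. The remark on hospital infrastructure is a general comment on the methods. It says nothing about how PITCH centres allocate treatment or when they reoperate. A reader might infer that the planned standard errors are certainly wrong; the text supports only that they can be.

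**The 80% is not a miscalculation.** This stands too. A reader might infer that the planned ANCOVA has less than 80% power. In the simulations its rejection rate under the alternative stays near 80%, and its defect is excess false positives. The loss of power belongs to the analysis that handles centre. One test does not suffer both faults.

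**The analysis plan may handle centre.** The Discussion says that a pre-specified plan exists, its list of covariates is illustrative, and the four-group, age-only model is described as a sample size input. This stands only in part. The article also states an age-adjusted primary objective and gives the denominator degrees of freedom. If the unseen plan includes centre, F(3,174) and the 80% do not describe that analysis, and the article still needs correcting.

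**Conclusion.** The point holds in conditional form. The primary model and sample size, as stated, ignore a factor that helps choose treatment and may also affect the outcome. At an assumed ICC of 0.05–0.10 with about 20 centres, type I error is about 5–8% under moderate and 9–15% under strong clustering of treatment, and 13–24% only with one treatment per centre. Power with centre fixed effects is then about 65–72% (moderate) and 32–45% (strong).

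These figures rest on assumed ICCs, assumed treatment mixes and a normal outcome for most runs, so they are indicative. Fixed effects are also the costlier way to adjust: under clustered treatment they lose power even at ICC 0 (0.632 moderate, 0.453 strong). A random intercept would normally lose less. The direction is clear in all clustered settings tried: the centre-adjusted analysis fell below 80%. The plan should be changed, but the article does not show that the result will be invalid.

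**What to change.** - Include centre in the primary model, by a random intercept or by cluster-robust standard errors with a small-sample correction. Robust errors deal with correlation only, and a random intercept removes confounding by centre only in part. A sensitivity analysis that splits each arm effect into within-centre and between-centre parts would address the rest; it is optional and will be imprecise with about 20 centres.
- State which centre is modelled for children whose hydrocephalus was first treated elsewhere: the treating or the enrolling one.
- Say that the 80% holds for independent patients, and give power over a stated range of ICC and of centre treatment mix.

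The centre identifier is already collected, so the model change needs only wording. The price is wider intervals and a less favourable stated power. If strong clustering is thought likely, the restated power may reopen the question of sample size.
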